#### Functional MRI data analysis

The fMRI data will be analyzed with SPM12 software (Wellcome Department of Imaging Neuroscience, London, UK), MATLAB_R2018a (Mathworks, Inc., Natick, MA, USA), DPARSF_V2.2 (http://www.rfmri.org/DPABI), and Freesurfer (http://surfer.nmr.mgh.harvard.edu/) software. Original data will be corrected; slice timing, affine head motion, and nonbrain extraction, spatial smoothing and temporal filtering will be applied.

Baseline ReHo and amplitude of low-frequency fluctuations (ALFF) values and functional connectivity maps from the real and sham acupuncture groups and the healthy control group will be compared using independent *t* tests. Independent *t* tests will be used for comparison of ReHo or ALFF values from the two groups after acupuncture. Paired *t* tests will be used to compare the pre-acupuncture and post-acupuncture data within each group. Average time series data from significant areas will be extracted to test the regional relationship with the rest of the brain using voxel-based general linear modeling. Fisher’s R-to-Z transformation will be applied to compare resting state functional connectivity using independent-sample *t* tests between groups [34].

Pearson’s correlation analyses will be performed to evaluate the relationship of clinical symptoms with ReHo or ALFF values in regions demonstrating significant differences between groups.

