## Background

Insomnia, which affects 10 to 15% of the population [1], is characterized by problems falling asleep, remaining asleep, or obtaining refreshing sleep, and is accompanied by impairments of daytime functioning [2]. However, the pathophysiology of insomnia is still under investigation. The most compelling hypothesis for insomnia is the hyperarousal model [3], which states that somatic, cognitive, and brain activation are increased in patients with insomnia [4].

The first-line therapies for insomnia are pharmacologic intervention with hypnotic medications and cognitive behavioral therapy. However, many patients are troubled by the side effects of medications, including lingering daytime sedation, cognitive impairment, and medication dependence. Psychotherapy is time-consuming and depends on the availability of trained therapists [5]. These factors lead to a low compliance rate for insomnia therapy [6]. Therefore, some patients have sought alternative treatments. Acupuncture, a critical component of traditional Chinese medicine, may relieve the symptoms of insomnia [7–10]. Nevertheless, the underlying neural basis for the effects of acupuncture remains largely unknown.

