### Trial design

This study will be conducted as a single-center, prospective parallel group, patient- and assessor-blinded, randomized controlled trial. The trial will be conducted in accordance with the Consolidated Standards of Reporting Trials [18] and Standards for Reporting Interventions in Clinical Trials of Acupuncture principles [19] to fulfill adequate reporting standards for randomized controlled trials. Sixty patients with insomnia disorder will be assigned to either a real acupuncture group or a sham acupuncture group, using a digital randomization table in a 1:1 ratio. Participants will keep a sleep diary at baseline, during week 4 of treatment, and during week 8 of the follow-up period. Both the neuropsychological measurements and fMRI scans will be performed at baseline, after completion of the acupuncture treatments, and at the conclusion of the follow-up period. Thirty age- and sex-matched healthy individuals who sleep well will be recruited as controls for the fMRI data analysis. All outcome measures will be performed once for the healthy control patients (Fig. 1).

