### Functional MRI scanning procedure

The rs-fMRI data will be obtained with a Siemens TRio 3.0 Tesla MRI scanner in Beijing Hospital of Traditional Chinese Medicine. All rs-fMRI images will be taken from a contiguous echo planar imaging template under the following conditions: 33 axial slices, repetition time = 2000 ms, echo time = 30 ms, thickness/gap = 3.5/0.6 mm, field of view = 220 × 220 mm^2^, flip angle = 90°, and matrix size 64 mm × 64 mm with 240 volumes. All participants will receive the following instructions: stay awake, do not move, close your eyes, and do not try to think about anything. For an anatomic reference, T1 images will be obtained before resting state scans.

The real acupuncture and sham acupuncture groups will be examined three times (before treatment, after treatment, and in the follow-up period.) and the healthy controls will be examined only once.

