#### Quality control

To ensure a standard operation procedure, acupuncturists will consistently apply acupuncture with the correct acupoints and manipulation. Investigators will attend training to properly apply the randomization number table, to make the diagnoses, to understand the inclusion and exclusion criteria, and to complete the case report forms. In addition, the fMRI scan will be performed with the same scanner and operator. Patients will be asked to close their eyes during the entire scanning procedure and stay still but not sleep.

Additionally, the Scientific Research Supervision group of the Beijing Hospital of Traditional Chinese Medicine will monitor the study regularly to ensure adequate recruitment rate, data accuracy, and data validity.

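### The imaging comparison of insomnia patients with non-randomized healthy controls uses unadjusted t tests, so any group difference in residual head motion can appear as a brain difference.

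*Protocol article*

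**What the plan says.** All references are to the protocol article.

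- **Preprocessing** (Functional MRI data analysis): "slice timing, affine head motion, and nonbrain extraction, spatial smoothing and temporal filtering will be applied". Realignment of head position is the one motion step named.
- **Baseline comparison** (same section): ReHo, ALFF and connectivity maps "from the real and sham acupuncture groups and the healthy control group will be compared using independent" t tests. The Discussion makes clear that one purpose is to compare insomnia patients with healthy controls.
- **Between arms after treatment** (same section): independent t "tests will be used for comparison of ReHo or ALFF values from the two groups after acupuncture".
- **Connectivity** (same section): the Fisher "transformation will be applied to compare resting state functional connectivity using independent-sample" t tests.
- **Controls** (Trial design): "Thirty age- and sex-matched healthy individuals who sleep well will be recruited as controls for the fMRI data analysis".
- **Conduct in the scanner**: all participants are told to "stay awake, do not move, close your eyes, and do not try to think about anything" (Functional MRI scanning procedure). Quality control adds: "Patients will be asked to close their eyes during the entire scanning procedure and stay still but not sleep".
- **Disease model** (Background): the hyperarousal model holds that "somatic, cognitive, and brain activation are increased in patients with insomnia". Patients must also score over 32 on the Hyperarousal scale to enter; no such score is set for controls.

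**The concern.** Realignment puts the head back in the same position from volume to volume. It does not remove the signal change that movement leaves in the realigned images. That change is partly shared by neighbouring voxels, and shared signal is what ReHo and connectivity measure. A group that moves more can therefore show higher values without any difference in brain activity.

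The comparison most exposed is patients versus healthy controls. Randomization does not balance these groups, and matching covers age and sex only. Patients are selected for hyperarousal, so a difference in stillness is plausible, though the documents do not report one. A t test has no place for a motion term. Adding one means changing the stated method, not filling in a detail.

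The Discussion takes higher ReHo and ALFF as a sign of hyperarousal, so an artefact in that direction would look like the expected finding. It would also carry forward. Regions found significant supply the time series for the connectivity analysis, and regions that differ between groups are the ones correlated with clinical symptoms.

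**Working it through.** The plan gives no figure for head motion, so there is none to reproduce. The check asks how often an unadjusted t test would reject when there is no true brain difference.

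**Inputs from the article**
- 30 patients per arm, 60 in all, and 30 healthy controls.
- Two-sided 5% level. This is stated under Clinical data analysis and assumed here for the imaging tests.

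**Assumed inputs** (shown as ranges)
- r, the within-group correlation of the imaging measure with residual motion: 0.2, 0.3, 0.5.
- D, the group difference in motion in within-group SDs: 0, 0.3, 0.5, 0.8.

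**Formulas**
- Measure = r × motion + √(1 − r²) × independent error, so the spurious shift in the measure is r × D SD.
- Noncentrality = r × D / √(1/n₁ + 1/n₂), with n₁ + n₂ − 2 degrees of freedom.
- The rejection probability is the two-tailed noncentral t probability beyond the 5% critical value.

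**One case in full.** For 60 v 30, √(1/60 + 1/30) = 0.2236. With r = 0.5 and D = 0.5 the shift is 0.25 SD and the noncentrality is 0.25 / 0.2236 = 1.12 on 88 degrees of freedom. The test rejects in 19.8%.

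**Results, one test at nominal 5%, no true difference**

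| Comparison | D | r = 0.2 | r = 0.3 | r = 0.5 |
|---|---|---|---|---|
| 60 v 30 | 0.3 | 5.8% | 6.8% | 10.2% |
| 60 v 30 | 0.5 | 7.3% | 10.2% | 19.8% |
| 60 v 30 | 0.8 | 10.9% | 18.6% | 42.5% |
| 30 v 30 | 0.3 | 5.6% | 6.4% | 8.8% |
| 30 v 30 | 0.5 | 6.7% | 8.8% | 15.9% |
| 30 v 30 | 0.8 | 9.4% | 15.0% | 33.2% |

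At D = 0 every entry is 5.0%. The 60 v 30 rows pool both patient arms against controls; the 30 v 30 rows apply if each arm is compared with controls separately. At a stricter level of 0.001, the 60 v 30 rates are 0.0014 to 0.0042 at D = 0.3, 0.0022 to 0.0137 at D = 0.5 and 0.0047 to 0.0598 at D = 0.8. A stricter level lowers the absolute rates, but the proportional inflation is larger.

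**After the fix.** With motion as a covariate the shift r × D is removed and the rate returns to 5%, for one degree of freedom. This follows from theory and was not simulated. It assumes that motion acts linearly and is measured well.

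**The case against.** **The preprocessing sentence is abbreviated.** It also leaves out spatial normalization to a common template, which voxel-wise group maps need. Nuisance regression, censoring of volumes and motion limits may well be in the full protocol. This stands: a reader might infer that motion is handled by realignment and nothing else, but silence in a condensed article does not show that. It does not reach the group tests, which the article names and which take no covariate.

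**The link from hyperarousal to head movement is inference.** Somatic activation is not movement in the scanner, and no section says patients move more. Participants are told to keep still, one scanner and operator are used, and both patients and controls with restless leg syndrome, diagnosed anxiety or claustrophobia are excluded. This stands as a reason to expect a modest difference. These measures reduce motion; they neither measure it nor adjust for it.

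**The treatment comparison is better protected.** A reader might infer that the plan cannot tell a treatment effect on the brain from calmer patients lying stiller. The documents do not support that. The arms are randomized and patients blinded, so motion differs systematically after treatment only if treatment or dropout changes it. Post-treatment motion is then a post-randomization variable, and adjusting for it could remove part of a real effect.

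**Larger error rates are tempting.** A shift of 0.3 SD in the measure itself would make the test reject in 21% (30 v 30) or 26% (60 v 30), and 0.5 SD in 48% or 60%. The arithmetic is right, but reading these rates off a simulated full-artefact shift assumes that one group carries the whole artefact and the other none. On the model above, a 0.3 SD shift needs D = 0.3/0.5 = 0.6 even at the highest assumed correlation, and D = 0.3/0.2 = 1.5 at the lowest.

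**Conclusion.** The point holds for patients versus healthy controls. The article fixes an unadjusted test for a non-randomized comparison in which residual motion is a plausible confounder, and a better method is available from data the pipeline already produces.

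For 60 v 30 the rejection rate rises from 5% to about 6% to 20% for motion differences of 0.3 to 0.5 SD, and to 11% to 43% at 0.8 SD. These figures rest on assumed values of r and D, on a linear effect of motion and on a 5% level per test. The inflation is small unless the groups clearly differ in motion, and the article states no report of motion by group from which a reader could judge.

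The documents support neither a claim that motion goes otherwise uncorrected nor a claim that the real-versus-sham imaging result is confounded. The point concerns secondary, exploratory imaging outcomes and the mechanistic objective. The PSQI primary outcome is not touched.

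**What to change.** In the section Functional MRI data analysis:

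1. For patients versus healthy controls, replace the independent t tests of ReHo, ALFF and connectivity with a linear model containing group and each scan's mean frame-wise displacement, taken from the planned realignment.
2. State that the realignment parameters are regressed from each voxel series before the measures are computed, if the full protocol does not already do so.
3. Report mean displacement by group and visit.
4. For real versus sham after treatment, keep the unadjusted comparison as the main one. Show the motion-adjusted result beside it as a sensitivity analysis, because treatment may itself affect motion.

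The cost is analysis wording, one covariate in the group model and a few degrees of freedom per scan. No new data are needed. The covariate can cost a little precision when motion differs between groups. For 60 v 30 with D = 0.8, the variance of the group difference is multiplied by 1 + (1/3)(2/3)(0.8²) = 1.14 and by the residual variance 1 − r². At r = 0.2 this is 1.14 × 0.96 = 1.10, a net loss; at r = 0.5 it is 1.14 × 0.75 = 0.86, a net gain. Six participants had been recruited when the article was submitted, so at that stage the change could be made before analysis.

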### Hypotheses

We hypothesize that sleep quality will be significantly improved in the group receiving acupuncture treatment compared with the sham group, as assessed by both subjective (PSQI) and objective (actigraphy) measurements.The hyperarousal state, measured by HAS, will be decreased more in the group receiving acupuncture than the sham group.Based on fMRI examination, functional connectivity and ReHo in the emotion-related areas will be altered in the group receiving acupuncture compared with the sham group.

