## Discussion

The purposes of the trial are to determine the effectiveness of acupuncture for the treatment of insomnia disorder and explore the potential neural mechanisms by which acupuncture affects sleep quality using neuropsychological measurements and rs-fMRI methods.

Based on the hyperarousal hypothesis, we will investigate the effect of acupuncture on spontaneous activities and functional connections in abnormal brain regions. The hyperarousal state was not assessed with fMRI analyses in previous clinical trials. To the best of our knowledge, this is the first randomized controlled trial associating the effects of acupuncture on insomnia disorder with its effects on brain hyperarousal state measured with rs-fMRI methods. The trial will provide important data on the effect of acupuncture and its possible mechanistic associations.

The influence of acupuncture on spontaneous regional brain activity and functional connectivity in patients with insomnia disorder will be explored using ALFF, ReHo, and functional connectivity analyses. ALFF [35] and ReHo analyses are simple, easily implemented methods which exhibit favorable test–retest reliability and have been successfully applied to insomnia research. Increased information processing in the emotion-related regions, manifested as higher ReHo and ALFF scores, suggest an association with the hyperarousal state of insomnia disorder [13–16]. However, the results of the previous studies have not been consistent enough to yield any general conclusions. Thus, we included a healthy control group. Baseline ReHo and ALFF values and functional connectivity maps from the patients with insomnia and the healthy control group will be compared to explore the characteristics of brain regions in patients with insomnia disorder.

In a recent study, acupuncture therapy decreased hyperarousal level and improved sleep quality in patients with insomnia disorder [9]. We speculate that this effect may have relevance to the modulation of regional brain activity and functional connectivity, especially in emotion-related areas. If our hypothesis is correct, ALFF and ReHo values and functional connectivity maps of the emotion-related regions will be modulated more in the group receiving acupuncture than in the sham group. These results will provide insight into the potential intrinsic mechanism of acupuncture for treating insomnia disorder.

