Long-term effectiveness is an important feature of the ideal treatment for insomnia. We found that verum acupuncture exhibited long-term effects in the follow-up period compared with sham acupuncture in patients with insomnia [23]. The possible neurobiological basis of the long-term effects is not well understood. Acupuncture may induce a long-term regulatory effect on brain function. In our trial, all patients will undergo fMRI during the follow-up period. One of the greatest strengths of the present study is the investigation of the long-lasting effects of acupuncture on insomnia and the central mechanism of the long-term effects of acupuncture.

Actigraphy will be applied in our trial to assess the changes in sleep quality. Although actigraphy may not be as accurate as polysomnography, this method can provide an accurate estimate of typical sleep duration. Actigraphy is more accepted and well tolerated by patients with insomnia disorder. Furthermore, actigraphy can record sleep in the patients’ natural environment and decreases the interference of factors that change a patient’s characteristic sleep patterns [36]. Meanwhile, sleep diaries and questionnaires will be recorded at the same time as the actigraphy. At follow-up, rs-fMRI and actigraphy analyses will be performed to provide objective measures related to the long-term alterations of sleep quality and brain function in insomnia disorder.

The design of an appropriate control group for a clinical trial is critical. However, it is difficult to use placebo needles for controls. Thus, we will use acupoints in the sham acupuncture group that are considered ineffective for insomnia according to our clinical experience. The possible nonspecific physiological reactions induced by needle pricking will be minimized by superficial puncturing and no manipulation to avoid the De qi sensation, which is believed to be fundamental to the efficacy of acupuncture.

The acupuncturists will receive training for consistent practices, including acupuncture point location and manipulation, to achieve effective quality control.

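### The between-arm fMRI test ignores each patient's baseline scan, and the only tests of change are within-arm paired t tests that cannot show more modulation under real than sham acupuncture

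*Protocol article*

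**What the plan says.** The Functional MRI data analysis section of the protocol article names these tests:

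- **Baseline:** independent t tests of ReHo, ALFF and connectivity maps across the real, sham and healthy groups.
- **Between arms after treatment, ReHo and ALFF:** independent t "tests will be used for comparison of ReHo or ALFF values from the two groups after acupuncture".
- **Within arm:** paired t "tests will be used to compare the pre-acupuncture and post-acupuncture data within each group".
- **Connectivity:** a Fisher "transformation will be applied to compare resting state functional connectivity using independent-sample" t tests between groups, with no time point given.
- **Association:** Pearson correlations with clinical symptoms.

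The third item under Hypotheses is that "functional connectivity and ReHo in the emotion-related areas will be altered in the group receiving acupuncture compared with the sham group". The Discussion words the expected result as a difference in change: ALFF, ReHo and "functional connectivity maps of the emotion-related regions will be modulated more in the group receiving acupuncture than in the sham group".

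Under Functional MRI scanning procedure, the two patient groups "will be examined three times (before treatment, after treatment, and in the follow-up period". The Discussion counts among the study's main strengths the "investigation of the long-lasting effects of acupuncture on insomnia and the central mechanism of the long-term effects of acupuncture", and it says that follow-up rs-fMRI analyses will be done. The repeated-measures analysis of variance stands under Clinical data analysis, and its pairwise step concerns questionnaire scores. It does not cover the imaging.

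**The concern.** The expectation that real acupuncture modulates brain activity more than sham is a between-arm contrast. The only listed tests that look at change work inside one arm at a time. A pair of such tests invites the reading that a significant change in real and a non-significant change in sham shows a difference. It does not, because two arms with the same true change often fall on opposite sides of the 5% line.

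The test that does compare the arms uses post-treatment ReHo or ALFF alone and leaves out the baseline scan. In a trial of 30 per arm this gives up precision that has already been paid for. The follow-up scan, which carries the long-term mechanistic aim, has no test assigned in the section that lists the tests. At stake is how reliable and how sensitive the mechanistic conclusions are.

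**Working it through.** The plan gives no imaging effect size, variance or sample-size calculation (Sample size section), so there is no figure of its own to reproduce. The inputs are 30 per arm and two-sided 5% from the article. The standardised change, the pre-post correlation r and the between-arm difference are assumptions, shown over a range.

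**1. What two paired tests show when the arms do not differ.** Let both arms have the same true mean change, dz, in units of the standard deviation of the within-patient change. Let p be the power of one paired t test at n = 30. The arms are independent, so:

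- P(exactly one arm significant) = 2p(1 − p)
- P(real significant, sham not) = p(1 − p)

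| dz | p | Exactly one significant | Real yes, sham no |
|---|---|---|---|
| 0.3 | 0.355 | 2 × 0.355 × 0.645 = 0.46 | 0.229 |
| 0.4 | 0.563 | 2 × 0.563 × 0.437 = 0.49 | 0.246 |
| 0.5 | 0.754 | 2 × 0.754 × 0.246 = 0.37 | 0.185 |

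A simulation (20,000 runs, r = 0.6) gives disagreement of 9%, 30%, 49%, 37% and 20% at dz = 0, 0.2, 0.4, 0.5 and 0.6. Real significant with sham not ranges from 4.5% to 25%. In the same runs, the direct between-arm tests reject in 4.8% to 5.1% (post-treatment values) and 4.7% to 5.1% (change scores), as they should. With 26 per arm, disagreement peaks at about 50%.

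**2. Precision of the between-arm test.** Take equal variances at both scans and set the variance of the post-treatment value to 1. The variance per patient that enters the between-arm contrast is then:

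- post-only: 1
- change score: 2(1 − r)
- baseline as covariate: 1 − r² (leaving aside the small cost of estimating the slope)

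| r | Post-only | Change score | Baseline-adjusted |
|---|---|---|---|
| 0.3 | 1 | 1.40 | 0.91 |
| 0.5 | 1 | 1.00 | 0.75 |
| 0.7 | 1 | 0.60 | 0.51 |
| 0.8 | 1 | 0.40 | 0.36 |

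The change score beats post-only only when 2(1 − r) < 1, that is r > 0.5. The adjusted test is never worse than either, apart from the slope cost.

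**3. What that means for power.** Assume a true real-versus-sham difference of 0.6 SD and 30 per arm, by the normal approximation:

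| r | Post-only | Change score | Baseline-adjusted |
|---|---|---|---|
| 0.3 | 0.64 | 0.50 | 0.68 |
| 0.5 | 0.64 | 0.64 | 0.77 |
| 0.7 | 0.64 | 0.85 | 0.90 |
| 0.8 | 0.64 | 0.96 | 0.97 |

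**4. The follow-up scan.** The scanning section schedules three scans for patients. The analysis section speaks only of baseline, pre-acupuncture and post-acupuncture data, plus a connectivity comparison with no time point. The Discussion promises follow-up imaging analyses. The sections do not contradict each other, but the list of tests stops one visit short of the stated aim.

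**The case against.** Four points can be made for the plan.

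- **It does compare real with sham.** A reader might infer that the plan never tests whether the brain effect differs between arms. That is too strong. Allocation is random, so the expected baseline difference is zero, and the post-treatment difference estimates the same effect as the difference in change. Chance baseline imbalance adds variance, not bias, and the 5% error rate already allows for it. This objection stands, and what remains against the post-only test is lost precision.
- **It nowhere says that a split result will count as evidence.** A reader might infer that false mechanistic claims are likely. The article states no such rule, and paired maps can be purely descriptive. The 37% to 49% counts both directions and applies to one test with a common non-zero change and no dropout. It shows what the paired tests cannot support, and does not forecast the trial's conclusions. The objection stands to that extent, but the article gives the paired tests no stated role although they are its only tests of change.
- **The third scan is not unused.** The Discussion says it will be analysed, and an analysis plan that is not shown may name the test. This stands: the scan lacks a named test in this document, and no more than that can be said.
- **The precision gain depends on an unknown r.** True. The Discussion credits ALFF and ReHo with good test–retest reliability, which points away from a low r, but it gives no figure.

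This is nevertheless more than detail left to another document. The article names specific tests by type and time point, and better ones are available from the same scans.

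**Conclusion.** The point holds in a limited form. The stated between-arm test for ReHo and ALFF is valid but leaves out the baseline scan. Relative to a baseline-adjusted test its variance is larger by a factor of 1/0.75 = 1.33 at r = 0.5 and 1/0.51 = 1.96 at r = 0.7, both values of r being assumed. The only stated tests of change are within-arm and should carry no between-arm inference. With equal true changes of 0.3 to 0.5 (assumed, 30 per arm), they disagree in 37% to 49% of cases, about 18.5% to 25% in the direction that would flatter real acupuncture. The follow-up scan needs a named contrast so that the analysis section matches the scanning schedule and the Discussion. fMRI is secondary and exploratory, and neither the PSQI primary analysis nor the sample size is affected. The change is worth making because it improves on the stated method at almost no cost.

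**What to change.** In the Functional MRI data analysis section:

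1. Make the inferential test a between-arm comparison of post-treatment ReHo, ALFF and functional connectivity, with the patient's baseline map as covariate. Prefer this to a plain change score, which is less precise than the post-only test when r is below 0.5. Give the connectivity comparison its time point.
2. Apply the same baseline-adjusted contrast to the scan taken eight weeks after the end of treatment.
3. Keep the paired pre-post tests as description within each arm, and state that a difference in significance between arms will not be read as a difference between real and sham.

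The cost is a change of wording and some extra modelling. It needs no further scans, visits or patients. The Trial status section reports six participants recruited at submission, so the change could be fixed well before any comparison of the arms.
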